## Abstract

During pregnancy, women are more inclined to modify their habits and lifestyle to find a new balance and promote well-being for themselves and the child-to-be. However, the availability of nutritional and psychological support is often limited by stigma, geographic barriers, and a lack of services. Digital health tools are emerging as possible solutions to cover these needs. This study explores the acceptability, feasibility, and user experience of Demetra, a virtual coach based on Acceptance and Commitment Therapy (ACT), designed to promote healthy lifestyles and mental well-being. Fifty pregnant women will be enrolled in the feasibility study of the intervention. It starts with an educational part on the foundations of healthy eating and suggestions about lifestyle habits, followed by a six-week psychoeducational module. Content is delivered through text, audio, and video formats. User experience and engagement will be measured through validated questionnaires and semi-structured interviews. Psychological well-being will be evaluated both before and after the program. The intervention is expected to be well-received, with high levels of satisfaction and engagement, leading to a greater awareness of healthy behaviors, improved psychological flexibility, and enhanced overall well-being. Demetra offers an accessible solution to support women through the transformative experience of motherhood with a multidisciplinary and innovative approach.

## 1. Introduction

### 1.1. Overview

It is becoming increasingly evident that lifestyles and exposure to risk or protective factors can profoundly impact health, interacting with genetic predisposition to determine medium- and long-term outcomes [1,2,3].

For instance, inadequate nutrition during pregnancy, lack of breastfeeding, or exposure to toxic substances and environmental pollutants may contribute to the development of metabolic disorders and obesity in adulthood. Awareness of these factors is critical, as they represent a public health priority [4]. Early intervention during pregnancy is essential, not only to mitigate future risks for both the mother and the infant but also as a unique opportunity to promote lifestyle improvements within the family, thereby establishing the foundation for long-term health.

Regarding weight, women who become pregnant while overweight or obese have a higher risk of complications during pregnancy and childbirth. These include the risk of impaired glucose tolerance, gestational diabetes, miscarriage, pre-eclampsia, thromboembolism, and maternal death. An obese woman is more likely to experience induced labor, prolonged labor, instrumental delivery, cesarean section, or postpartum hemorrhage; labor may also require higher doses of pain relief, which can be difficult to administer in obese conditions. There is also a greater likelihood of requiring general anesthesia, and after delivery, wound healing may be slower, with an increased risk of infection. Additional breastfeeding support may also be necessary due to challenges such as difficulty in latching the infant. Obese women may also have fewer options regarding where and how to give birth.

Children born to overweight or obese women also face various health risks. These include a higher probability of fetal death, stillbirth, congenital abnormalities, shoulder dystocia, macrosomia, and subsequent obesity [5,6]. The analysis of data available for the period 2015–2019 shows that the same situation applies to the population of women living in Trentino [7]. In fact, this study demonstrates that maternal excess weight and obesity are linked to a higher risk of gestational diabetes, gestational hypertension, pre-eclampsia, cesarean section, induction, postpartum bleeding, fetal macrosomia, and the need for neonatal resuscitation and NICU hospitalization. Additionally, infants born to overweight and obese mothers were less likely to be breastfed. Developing and implementing public health initiatives focused on preventing excessive weight gain during reproductive age could substantially improve both maternal and fetal health outcomes.

Cognitive Behavioral Therapy (CBT) techniques, particularly those related to third-wave therapies, have been shown to be more suitable than other psychotherapeutic approaches for being adapted into low-intensity interventions delivered through non-traditional methods such as e-health applications. This protocol, specifically, is based on the principles of Acceptance and Commitment Therapy (ACT), a third-wave form of CBT [8,9].

In developing this protocol, we conducted a thorough review of the scientific literature related to ACT in general and its application to individuals who are overweight or obese. ACT is a therapeutic approach based on two key concepts: acceptance (learning to accept thoughts by recognizing them as part of the human experience) and commitment (identifying what is important, one’s values, and taking action in that direction). It combines mindfulness practices with cognitive interventions aimed at increasing psychological flexibility—the ability to act effectively even in the presence of emotions or sensations perceived as negative [8,9].

The ACT approach proposes the use of a practical tool known as the matrix, which aims to help individuals visualize and better understand their feelings and act according to their values. The matrix is used throughout the intervention to facilitate awareness and psychological flexibility, as it helps individuals make choices based on their values rather than reactively responding to distress [2]. Regarding the application of the ACT model to overweight or obese individuals, a thorough review of several manuals was conducted, highlighting the potential of this approach for people with these physical characteristics. The adoption of the ACT model involves a reversal of the common paradigm, which includes a series of “quick fixes” or even “effortless weight loss”, focusing, instead, on providing space for the various processes that characterize the model: acceptance of negative thoughts, discomfort, and setbacks, not by fighting them but by learning to live with them; cognitive defusion from negative thoughts, which entails learning to distance oneself from invalidating thoughts; committed action, encouraging individuals to identify their values and act upon them; being in the present moment, through mindfulness, to increase focus on the present; self-compassion, learning to be kind to oneself in the face of potential mistakes. In summary, the literature review highlighted several studies that support the effectiveness of ACT in weight loss and weight reduction [10,11,12,13].

Therefore, the decision was made to divide this protocol into six sessions, each addressing one of the six core principles of the ACT model: values, committed action, acceptance, present moment contact, and self as context.

This study aims to design a digital health intervention through a virtual assistant (named Demetra and described in the following) available on mobile devices for providing women with initial information and suggestions about healthy habits during pregnancy, and then an ACT-based psychoeducational session to support the adoption of healthy lifestyles.

### 1.2. Local Background

The Autonomous Province of Trento (PAT) is committed to promoting community welfare by offering preventive, protective, and curative interventions dedicated to the whole pregnancy up to the first thousand days of the child’s life that are delivered through digital health tools [4].

In this context, the “Birth path-Dedicated midwife” is the set of services accompanying the birth event to guarantee information, education, counseling, and screening that is offered to promote and monitor the well-being of the mother, the newborn, and the family as a whole, and to promote the continuity of the care provided and pre-/post-natal assistance. The program is aimed at women who are pregnant, or who are trying to get pregnant, residing in the Province of Trento, and is provided according to the relevant territorial service. The timely care of the woman is guaranteed, and all necessary checks are scheduled from the beginning of the pregnancy to the end of the puerperium. According to the “Partnership caseload midwifery care” model, the midwife works in collaboration with the gynecologist, the general practitioner, the primary care pediatrician, and any other specialist involved in supporting the care before, during, and after childbirth based on the clinical condition of the woman. The Autonomous Province of Trento and the Provincial Healthcare Services (APSS) obtained the UNICEF-Baby Friendly Initiative accreditation in 2022, both for birth points and for the community. The birth point in Trento has been recognized as “Friends of Children” since 2015 [14,15,16].

The annual report on birth rates for the year 2023 [17] shows that 92.4% of all women giving birth in the Province of Trento joined the birth process described above. Taking into consideration the BMI data, 18.0% of women who became mothers were overweight, and 8.2% were obese. The probability of being obese before pregnancy among foreign mothers is almost twice as high as that of Italian mothers (14.3% vs. 6.4%), and this proportion is similar for overweight cases (28.1% vs. 15.0%). Moreover, the percentage of mothers in obese or overweight conditions increases with decreasing educational qualifications. Regarding obstetric and neonatal pregnancy outcomes, obesity is a risk factor for complicated pregnancies, in particular for pre-eclampsia and gestational diabetes. Also, the mode of birth is significantly associated with obesity risk; in fact, 24.8% of obese mothers have cesarean sections compared to 19.1% of mothers with normal weight. There is also a significant relationship between maternal obesity and weight at birth: 6.4% of newborns from obese women have a weight greater than or equal to 4000 g, compared to 4.7% of newborns from mothers with normal weight [17,18,19,20].

The research project described in this article fits into this context.

The project is supported by the TrentinoSalute4.0 Digital Health Program, and it is promoted by the Department of Health and Social Policies of the Autonomous Province of Trento, in collaboration with the Provincial Health Services Company (APSS) and under the technical–scientific management of the Bruno Kessler Foundation (FBK).

### 1.3. Goal of the Study and Research Questions

The present study is positioned within the design and development cycle of the Obesity-Related Behavioral Intervention Trials (ORBIT) model [21], specifically in phase 1a–1b of co-design and refinement of the intervention with key stakeholders and phase 2a of preliminary validation of its feasibility. The intervention consists of delivering educational content in text, audio, and video formats through a virtual coach (i.e., a digital assistant) named Demetra, integrated within the TreC platform. Participants will be able to log their food intake in a digital diary and receive personalized feedback from the system, as well as monitor their weight by entering weekly measurements. This intervention is grounded in the framework of behavior change pathways [22], aiming to support women in developing adaptive strategies to promote both physical and psychological well-being. It is important to clarify that, in this context, the term intervention refers to an application (specifically, the virtual coach) that provides evidence-based content at scheduled intervals, in a predefined, rule-based, structured, and systematic manner. All materials are reviewed by professional psychologists to ensure their quality and appropriateness. This material is available for users in audio, text, and/or video formats, and can be managed autonomously; therefore, the virtual coach presents itself as a tool for the delivery of information according to appropriate time frames. The intervention is developed for research purposes only, in order to promote the improvement of women’s physical and psychological well-being, by means of the modules based on the principles of ACT, as described in Section 2.1.

#### 1.3.1. Primary Objective

The primary objective is the co-design of the intervention with the involvement of domain experts and representatives of the target users (overweight pregnant women) from the beginning, to ensure the correspondence of the intervention to their requirements and needs. Moreover, we are going to perform an exploratory investigation of the experience and the engagement of women interacting with Demetra inside the TreC Mamma application. Semi-structured interviews will allow us to investigate how people felt during the intervention.

#### 1.3.2. Secondary Objectives

The secondary objective is to assess the level of physical and psychological well-being pre- and post-intervention through self-report questionnaires. Furthermore, the weekly monitoring of weight will allow a user to compare her own weight gain with her own growth curve for reference.

## 2. Materials and Methods

### 2.1. The Demetra Intervention

Demetra has a double purpose: at the beginning, it will provide information and educational tools for a healthy lifestyle during pregnancy and for gaining awareness of your real habits; after that, it will deliver a digital intervention based on ACT techniques for promoting healthy lifestyles through a psychoeducational approach. The intervention is targeted at pregnant women of legal age with overweight conditions and a good knowledge of both written and spoken Italian. As for technical skills, the only requirement is knowing how to download and use mobile apps.

Only an overview of the initial educational part will be given in this article, preferring to delve deeper into psychological ACT-based intervention. After a profiling data collection, pregnant women have at their disposal a microlearning course on healthy eating education, a 7-day food intake diary (for becoming aware of your real habits and receiving personalized feedback), a tool for monitoring the gaining weight in relation to the growth curves for pregnancy (both single and twin) and information, videos, and infographics about safe physical exercises organized by trimester of pregnancy. All these resources are presented and proposed at the beginning and remain available at all times. They were defined and prepared in collaboration with a nutrition biologist, while the physical exercises were developed with the support of a kinesiologist, both of whom were experienced in working with overweight pregnant women.

Going on with the next psychological part, Demetra provides ACT-based psychoeducational sessions through dialogs and multimedia materials (in video, audio, and image formats); it also plays the role of a virtual coach that guides women in carrying out exercises and tasks assigned to be carried out independently between one session and another. The acceptability and feasibility are going to be evaluated at the end of a pilot study (Figure 1).

The Demetra chatbot design was performed by a group of psychologists with specific expertise in communication of the Digital Health Research Unit (DHRes) of FBK and the Istituto Pavoniano Artigianelli of Trento, in collaboration with an experienced ACT psychotherapist. Afterwards, a revision by a Senior Psychologist of the Psychology Operating Unit of APSS was performed. All dialogs, videos, and audio tracks adopt an educational approach and do not follow an emergency management logic.

The psychoeducational intervention has a total duration of six weeks and includes one session per week, approximately 15 to 20 min in length. The goal of this intervention is to enable women to increase their psychological flexibility, allowing them to acquire and maintain healthy lifestyles despite experiencing negative emotions or feelings. The program content was developed by a team of clinical psychologists, in the absence of a pre-existing format, from ACT principles and a selection of reference texts, including Healthy Habits Suck [1], The Diet Trap [3], and The ACT Matrix [2].

Efforts will be made to achieve this purpose through a gradual delivery of the scheduled content. The women will also be asked to perform tasks independently and to fill in their personal diary available in the app on a daily basis, with the aim of promoting psychological flexibility and awareness with regard to eating behavior.

It is emphasized that this is not a device to replace in-person psychological support, should it be necessary. For this reason, the possibility of referral to a health professional is reminded throughout the various sessions where repeated malaise is manifested by women. A central aspect of the program is the deconstruction of dysfunctional beliefs related to weight control and weight loss, which are frequently present in the participants’ experiences. These issues are addressed through defusion strategies, experiences of contact with one’s own values, and acceptance practices, in line with the principles of ACT.

In the co-design phase of the intervention, two focus groups will be conducted involving health system professionals with various domain expertise and representatives of the target users. The objective is to verify the correspondence, completeness, and appropriateness of the mode of content presentation to the actual needs and preferences of the prospective users.

Each focus group will involve 6–10 representatives of the target figures and will be moderated by an FBK facilitator who will collect feedback from participants based on the presentation of some initial prototypes of the intervention.

The duration of each focus group will be approximately one hour. The data collected will then be analyzed mainly with qualitative methodologies, such as thematic analysis, and will allow for refining the digital modes of delivery of the intervention (without going to change the content of the intervention itself) to increase its acceptability and future usability and effectiveness. Participation in the focus groups will be on a voluntary basis and explicit consent will be sought through the informed consent form.

Following this phase, another co-design pilot study was planned, involving various domain experts (psychologists, communication experts, and reference clinicians) and some target users, to test the prototype and provide feedback and suggestions to improve the intervention itself before the start of the main study.

### 2.2. Study Design and Plan

This research project combines the principles of co-design, where stakeholders and final users actively participate in the design process, with a proof-of-concept design phase, to assess the feasibility and initial effectiveness of the designed digital intervention. This type of study requires a small, diverse, and representative sample (overweight pregnant women, healthcare professionals, and researchers) to ensure that the final service is well-designed, user-friendly, and meets the needs of the target audience.

In the psychological component of the intervention, the virtual coach Demetra will engage with participants for a continuous period of six weeks, spanning from the 14th to the 24th week of pregnancy. At the beginning of the program, six self-report questionnaires will be administered, as described in the Collected Parameters section, to establish baseline levels. The intervention will then be delivered through a variety of formats, including text, images, audio, and video. At the conclusion of the program, the same questionnaires will be re-administered to evaluate potential changes in eating habits, psychological well-being, and perceived quality of life.

Additionally, four more questionnaires will be administered to assess usability aspects, specifically user experience (UX) and user engagement (UE). All data collection procedures comply with current Italian regulations concerning personal data protection.

One month after completing the intervention, participants who have provided informed consent will be invited to take part in a semi-structured interview. This qualitative phase aims to explore their experience using Demetra within the TreC Mamma app and to gain insight into their emotional and cognitive responses throughout the process.

### 2.3. Participant Recruitment and Withdrawal

The target population of the study includes all overweight pregnant women residing in Trentino.

The inclusion criteria for participation in the study are as follows: (a) being pregnant; (b) being between the 14th and 24th week of gestation at the time of enrollment; (c) being aged 18 years or older; (d) owning a smartphone with internet access and the ability to download and use the application; (e) being a resident of the Autonomous Province of Trento; (f) having a good command of written and spoken Italian; (g) having a pre-pregnancy Body Mass Index (BMI) between 25.00 and 29.99; and (h) following an omnivorous diet. The exclusion criteria are as follows: (a) inability to provide informed consent (a prerequisite for study participation); (b) insufficient knowledge of the Italian language; (c) diagnosis of type 1 or type 2 diabetes mellitus (as these participants are already on a specific diet); (d) diagnosis of gestational diabetes in the current or any previous pregnancy; (e) fasting blood glucose levels between 100 and 125 mg/dL prior to or at the beginning of pregnancy; (f) belonging to populations with a high familial prevalence of diabetes (e.g., individuals from South Asia, the Caribbean, or the Middle East); (g) current or past diagnosis of an eating disorder; (h) being under the care of a dietitian; and (i) history of bariatric surgery.

Recruitment will take place among pregnant women belonging to the pregnancy care services of the APSS of Trento. Convenience sampling will be used. Midwives and/or doctors from the hospital and territorial services of the APSS will be involved in identifying women who are potentially eligible to participate in the study.

The study will begin after approval is granted by the Territorial Ethics Committee for Clinical Trials of the PAT.

Once approved, the timeline for the study is going to be as follows: the recruitment phase will take three months, followed by enrollment and the subsequent start of the study. There will be three months of follow-up. The study will end as data collection is concluded, no later than two months after the end of the pathway. Recruitment will go on until the planned sample size is reached.

### 2.4. Sample Size Estimate

It was estimated that for this proof-of-concept study, it will be necessary to recruit 50 volunteer pregnant women. This sample size was determined considering that both parametric and non-parametric statistics will be performed.

According to Noether [23], when assuming a non-normal distribution, non-parametric statistical analyses require a sample size of 24 pregnant women, considering the Bonferroni correction (α = 0.025), desired statistical power, and appropriate effect size for non-parametric tests such as the Kruskal–Wallis test and Wilcoxon post hoc test [24].

If parametric statistical analyses are also planned (assuming a normal distribution), a sample size of 41 pregnant women is required, accounting for the Bonferroni correction (α = 0.025), with a statistical power of 0.80 and a significance level of 0.025. Considering a potential dropout rate of 20%, it is estimated that a total of 50 pregnant women should be recruited for the study.

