#### 2.6.2. Data Collection

Socio-demographic data will be collected using a pre-structured form at the time of enrollment by the midwives and doctors involved. Each participant will be given a unique alphanumeric code. This socio-demographic data sheet will be kept separately from the data collected during the study. The required socio-demographic data will be: (a) date of birth, (b) expected date of delivery, (c) level of education, (d) occupation, (e) marital status, (f) number of previous pregnancies and deliveries, (g) partner’s occupation, if applicable, (h) pre-pregnancy weight, and (i) height.

Women will also be asked if they would like to participate in focus groups and qualitative interviews one month after the intervention ends (Table 1). If they consent, they will be asked for a contact telephone number.

The psychoeducational path offered by Demetra begins and ends with the completion of self-report questionnaires, which takes approximately 15 min.

Specifically, six questionnaires will be administered at the beginning and end of the psychoeducational intervention to investigate depressive and anxiety symptoms, general well-being, experiential avoidance, psychological flexibility, and adherence to the Mediterranean diet. None of the questionnaires had a diagnostic purpose, so they will not be used to diagnose psychopathology, but only for the collection of descriptive data.

A further four questionnaires will be sent out during the course with the aim of analyzing usability and the woman’s involvement with the app and the virtual coach, Demetra. Specifically, the usability questionnaires will be administered at the end of the third (three questionnaires) and sixth (end of the study; four questionnaires) weeks.

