### 2.8. Data Analysis

#### 2.8.1. Quantitative Analysis

Statistical data processing will be conducted using R software, version 4.0.0 [42], IBM SPSS Statistics, version 27.0 [43], Stata 17 [44], and JASP, version 0.18.2 [45].

Categorical variables will be summarized using absolute and percentage frequency distributions, while quantitative variables will be described through appropriate measures of central tendency and variability.

Descriptive analyses will be conducted for both the physical–psychological variables (including depressive and anxiety symptoms, general well-being, experiential avoidance, psychological flexibility, physical activity, and eating habits) and the usability (UX) and user engagement (UE) variables. These analyses will be performed on data collected at the start, during, and at the conclusion of the interaction with Demetra.

The relationships between variables will primarily be examined using specific statistical tests such as the chi-square test, Fisher’s exact test, paired *t*-test, Wilcoxon’s non-parametric tests, and the sign test (depending on whether assumptions are met). This will help identify differences between baseline and post-intervention measurements within the same sample for the variables under study. Additionally, univariate logistic or multinomial regression models will be presented. To control for potential confounding variables, multivariate regression models will be employed, adjusting the effects of explanatory variables on outcome variables accordingly. A *p*-value ≤ 0.05 will be considered statistically significant for all analyses. Furthermore, McNemar’s test and Cochran’s Q test are planned for assessing paired qualitative data [46].

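### The two-test Bonferroni level of 0.025 behind the sample size is not the level used in the analysis: six outcomes are compared pre/post and each is judged at p ≤ 0.05

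*Protocol article*

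**What the plan says.** Section 2.4 gives two calculations.

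- Non-parametric: "non-parametric statistical analyses require a sample size of 24 pregnant women", after Noether, at a Bonferroni level of 0.025, with an "appropriate effect size for non-parametric tests such as the Kruskal–Wallis test and Wilcoxon post hoc test". Neither the power nor the effect size is given as a number.
- Parametric: "a sample size of 41 pregnant women is required". The error rates behind this figure are described as "accounting for the Bonferroni correction (α = 0.025), with a statistical power of 0.80 and a significance level of 0.025". The test and the effect size are not named.

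The larger figure sets recruitment: "Considering a potential dropout rate of 20%, it is estimated that a total of 50 pregnant women should be recruited for the study".

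Section 2.6.2 says that "six questionnaires will be administered at the beginning and end of the psychoeducational intervention". Table 2 lists them at week 0 and week 6: PHQ-9, GAD-7, GHQ, MPFI, MEDI-LITE and IPAQ. The Limitations section says that there is no control group.

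Section 2.8.1 lists chi-square, Fisher, paired t, Wilcoxon and sign tests, McNemar, Cochran's Q and regression models. Of the main group of tests it says: "This will help identify differences between baseline and post-intervention measurements within the same sample for the variables under study". Kruskal–Wallis is not listed. The same section sets p ≤ 0.05 as the significance threshold for all analyses and mentions no correction.

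**The concern.** A Bonferroni level of 0.025 is 0.05 divided by two. Nothing in the article says which two tests share the 5%, and the pre/post family has six members. The analysis section then uses 0.05 for every test. So 0.025 matches neither the number of outcomes nor the rule by which results will be called significant.

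A reader of Section 2.4 would take the pre/post results to be both powered at 80% and protected against multiplicity. Under Section 2.8.1 they have no such protection, and a chance finding on one of six scales could be reported as a significant improvement.

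The test named for the figure of 24 is also wrong for this design. Kruskal–Wallis compares independent groups, and post hoc tests separate those groups afterwards. Here there is one group measured twice.

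**Working it through.** **Inputs.** From Section 2.4: n = 41, α = 0.025, power 0.80, 20% dropout, 50 recruited. From Section 2.6.2 and Table 2: six pre/post instruments. From Section 2.8.1: threshold 0.05. Assumptions: two-sided tests, and a paired t-test as the parametric test. The effect size is back-solved.

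**1. Reproduce 41.** For a paired t-test with standardised change d, the test statistic follows a noncentral t with n − 1 degrees of freedom and noncentrality d√n. Setting n = 41, two-sided α = 0.025 and power 0.80 gives d = 0.497 (noncentrality 0.497 × √41 = 3.18). With d = 0.5, the smallest n is exactly 41 (power 0.805). The operative figure therefore fits a single paired comparison in one group.

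**2. From 41 to 50.** 41 × 1.2 = 49.2, rounded up to 50. With 20% lost, 50 × 0.8 = 40 women complete. Power is shown for 41 and 40.

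**3. Paired-t power per test at d = 0.497 (values at d = 0.5 in brackets).**

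| Level per test | n = 41 | n = 40 |
|---|---|---|
| 0.05 (Section 2.8.1 as written) | 0.874 (0.878) | 0.866 (0.869) |
| 0.025 (Section 2.4) | 0.800 (0.805) | 0.789 (0.793) |
| 0.05/5 = 0.01 | 0.683 (0.689) | 0.668 (0.674) |
| 0.05/6 = 0.0083 | 0.658 (0.664) | 0.643 (0.649) |

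The five-outcome row is there because Section 2.6.2 says the IPAQ refers to activity before pregnancy, so it arguably cannot register a change. If the 0.025 were one-sided, the implied d would be 0.448. Power at 41 and 40 would then be 0.880 and 0.873 at level 0.05, and 0.646 and 0.632 at level 0.05/6. The picture is the same.

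**4. Familywise error, independent tests: 1 − (1 − α)^k.**

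- Six tests at 0.05: 1 − 0.95^6 = 0.265.
- Six tests at 0.025: 1 − 0.975^6 = 0.141 (simulated 0.130 and 0.113 at correlations of 0.3 and 0.5).
- Five tests at 0.05: 1 − 0.95^5 = 0.226.
- Two tests at 0.025: 1 − 0.975^2 = 0.049. This is the only case in which 0.025 holds 5%.

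**5. The figure of 24.** Noether's signed-rank formula is n = (z₁₋α/₂ + z₁₋β)² / [3(p′ − 0.5)²], with p′ = Φ(d√2). At α = 0.025 and power 0.80 the numerator is 9.505.

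- d = 0.8: p′ = 0.871, so n = 9.505 / (3 × 0.371²) = 23.0, rounded up to 24.
- d = 0.5: p′ = 0.760, so n = 46.8, rounded up to 47.

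On this formula 24 needs an effect near 0.8, while 41 needs one near 0.5. Under these readings the two branches do not share an effect size.

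**The case against.** **The recruitment target does not rest on Kruskal–Wallis.** A reader might infer that the 50 was computed for the wrong test. It was not. That wording is attached only to the 24, and loosely, as an example. The 41 reproduces as a paired t-test, and the 80% is stated only for the 41. This stands in full.

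**The study is not planned at about 65% power.** A reader might infer that the true power is well below 80%. That figure arises only if Bonferroni is extended to six (or five) outcomes, which the article does not plan. Under the written 0.05 rule, power per test is above 80%. The defect as written is unprotected type I error, not low power.

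**Correction may be unnecessary here.** Pre/post well-being is a secondary objective (Section 1.3.2). The questionnaires are said to serve description (Section 2.6.2), and the Limitations section disclaims any evaluation of effectiveness. Uncorrected exploratory testing is a defensible choice in such a study, which limits the weight of the point. But Section 2.4 claims the correction, Section 2.2 includes initial effectiveness in the study's purpose, and Section 3 expects well-being to rise. A claimed correction should be applied or withdrawn.

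**A separate analysis plan could name the two tests.** It could, and the missing names alone would be no finding. The conflict between 0.025 in Section 2.4 and 0.05 for all analyses in Section 2.8.1 is in the article itself.

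**Conclusion.** The point holds as an inconsistency between the level used for sizing and the level used for analysis. As written, each paired comparison has about 87% power, and familywise error is about 26% for six independent tests. Positive correlation between the scales would lower the 26%. Using 0.025 for all six would still leave about 14%. Covering all six by Bonferroni would bring paired-t power to about 64–66% (about 67–69% for five). All power figures depend on a standardised change of about 0.5, which the article does not state.

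The Kruskal–Wallis and post hoc wording is a separate misdescription with no effect on the 41 or the 50. The matter is worth correcting before results are reported, but it concerns secondary outcomes of a feasibility study and does not call the recruitment target into question.

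**What to change.** In Section 2.4, replace the Kruskal–Wallis and post hoc wording with the planned paired comparison of week 0 and week 6, and state the effect size assumed. Then choose one of two routes.

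1. **Keep the correction.** Name in advance the two pre/post outcomes tested at 0.025 each, for example the MPFI, which Section 2.6.2 already calls the primary theoretical outcome, and one other. Change the p ≤ 0.05 sentence in Section 2.8.1 to match. Report the remaining outcomes as estimates with confidence intervals and no significance claim. The stated α and 80% power for 41 women then hold under the back-solved effect.
2. **Drop the correction.** Remove the Bonferroni claim from Section 2.4, describe all pre/post tests as exploratory and uncorrected, and restate the power at 0.05 (about 87% for a change of about 0.5).

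Replacing 0.05 with 0.025 in Section 2.8.1 without naming two outcomes would not be enough. Either route changes wording only. The 50 women and the data collected stay as planned. The cost is fewer significance claims under the first route, and the loss of the multiplicity claim under the second.
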